### Patients

2.3

Diagnostic criteria: ① Diagnosis of myocardial infarction in the fourth edition of the General Definition of Myocardial infarction in the European Society of Cardiology 2018^[11]^; ② According to the New York Heart Association (NYHA) cardiac function classification standard, cardiac function is grade I to III.

Inclusion criteria: ① Meet the diagnostic criteria for myocardial infarction; ② Age ≥35 years old and ≤80 years old; ③ Cardiac function grade I to III; ④ Stable condition after interventional surgery without serious complications; ⑤ Have a certain communication and understanding ability, express their wishes correctly; ⑥ After informed consent and signed an informed consent form, they voluntarily participated in this research project.

Exclusion criteria: (A standard for judging whether a patient can become a experimental object): ① Suffer from acute systemic disease; ② Cardiac function grade IV; ③ Risk stratification of cardiac rehabilitation in patients with coronary heart disease^[12]^ showed that they are at high-risk; ④ Relative or absolute contraindications for rehabilitation exercise such as blood pressure drop during exercise; ⑤ Limb dysfunction; ⑥ Complicated with severe mental illness; ⑦ Unable to understand the research plan after explanation or unwilling to participate.

Exclusion criteria: (A criterion used to screen patients who have become experimental subjects, but the relevant data cannot be included in the final data analysis): ① Severe adverse events or serious complications are not suitable for the next test; ② Poor compliance, which affects the judgment of efficacy and safety; ③ The disease progresses during the treatment process, and the treatment plan needs to be changed; ④ For any reason, the subject asked to withdraw from the trial.

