### Interventions

2.5

This study will select patients who meet the criteria of this study by recruiting in the hospital. A randomized controlled study will be used, in which the control group: conventional treatment; the experimental group: Tai Chi exercise will be added to the control group. The 2 groups of patients will receive the same routine care. During the trial period, avoid smoking, alcohol and irritating food, avoid strenuous exercise, and pay attention to adverse reactions. When necessary, the attending doctor can appropriately adjust the plan according to the patient's condition, and all intervention methods will be recorded in detail for the final result analysis. Efficacy assessors are not aware of the study group plan, and data statisticians are not involved in the design and implementation of the study. Before and after treatment, the health status of each patient will be evaluated, including the outcome indicators, and all patients will be followed up by telephone. Follow-up content includes cardiovascular events and rehospitalization.

Control group: according to the relevant guidelines after myocardial infarction intervention, standard drug treatments will be given, including antiplatelet drugs, statins, angiotensin converting enzyme inhibitors, nitrates, β-receptor blockers, and health education. The content of the education includes the control of myocardial infarction risk factors, techniques for improving sleep quality, diet guidance, etc, and pays attention to communicating with patients, mastering their psychological and emotional changes, and avoiding or alleviating bad moods such as anxiety and depression in elderly patients.

Experimental group: on the basis of conventional treatment, the experimental group will be given 24 simplified Tai Chi. Professional Tai Chi teachers will teach and practice the subjects to ensure that the practice time and movement rhythm are basically the same. The whole set of Tai Chi includes 3 parts: preparation activity, training activity and end activity, totaling about 20 minutes, twice a day, once in the morning and once in the afternoon, and lasts for 24 weeks.

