#### Efficacy indicators

2.6.1

Main efficacy indicators: total effective rate: referring to the “Guiding Principles for Clinical Research of New Chinese Medicines”,^[13]^ total effective rate = (marked effective number + effective number)/total number × 100%. According to NYHA grading method, evaluate the curative effect of cardiac function: ① Marked effective: cardiac function improved by more than grade 2; ② Effective: cardiac function improved by grade 1, but not as good as grade 2; ③ Ineffective: cardiac function improved less than grade 1; ④ Deterioration: the deterioration of heart function is less than grade 1.

Secondary efficacy indicators: 6 minutes walking test, brain natriuretic peptide, left ventricular ejection fraction, medical outcomes study short-form36 (SF-36).

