### Statistical analysis plan

2.9

The database is established by Excel. The full analysis set refers to the intent-to-treat analysis of all subjects randomly enroll, treat at least once and visit at least once. Per-protocol set: includes all subjects who comply with the trial protocol, have no missing baseline variables, and can measure the main variables. safety set: including random enrollment, at least 1 medication, and at least 1 safety visit after medication.

In this study, SPSS25.0 statistical analysis software will be used for data analysis. If the measurement data meet the normal distribution, the independent sample *t* test is used between the groups, and the paired sample *t* test is used within the group. The results are represented by ($\bar{X}\pm S$); Nonparametric test will be used for those who did not meet the normality, and the results will be expressed in quartiles; Chi square test will be used for counting data. The incidence of adverse events will be compared by chi square test. *P* *<* *.05*, with statistical significance.

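### Section 2.3 drops randomised patients from the final analysis for events after randomisation, which conflicts with the intent-to-treat set in section 2.9

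*Protocol article*

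**What the plan says.** Section 2.3 (Patients) has two exclusion lists. The first governs entry. The second is introduced as "A criterion used to screen patients who have become experimental subjects, but the relevant data cannot be included in the final data analysis". It has four items:

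- Item ①: severe adverse events or serious complications that make continuing unsuitable.
- Item ②: "Poor compliance, which affects the judgment of efficacy and safety".
- Item ③: "The disease progresses during the treatment process, and the treatment plan needs to be changed".
- Item ④: "For any reason, the subject asked to withdraw from the trial".

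Section 2.9 (Statistical analysis plan) states: "The full analysis set refers to the intent-to-treat analysis of all subjects randomly enroll", with the added conditions of at least one treatment and at least one visit. It separately defines a per-protocol set of patients who kept to the protocol. It does not say which set is used for the primary outcome.

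In section 2.5 (Interventions) both arms receive the same drugs, health education and routine care, and "Tai Chi exercise will be added to the control group" in the experimental arm: about 20 minutes, twice daily, for 24 weeks. In section 2.6.1 the primary outcome is the share of patients whose NYHA grade improves. Ineffective and deteriorated are outcome categories that do not count as success.

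**The concern.** All four grounds arise after randomisation, so removing these patients can undo the balance that randomisation created. Two features make this more than a formality.

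First, the Tai Chi arm has one more thing to comply with than the control arm, and a demanding one. Item ② is therefore likely to remove more patients there. If those who keep up the exercise tend to have better function, the Tai Chi success rate rises without any treatment effect.

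Second, item ③ removes patients because they got worse, whereas section 2.6.1 would leave such patients in the denominator as non-successes. If Tai Chi prevents progression, the rule deletes control failures and hides benefit. If Tai Chi causes progression, it deletes Tai Chi failures and hides harm. Item ① can act in the same way.

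A larger sample would not cure either effect.

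**Working it through.** **The conflict.** Take a Tai Chi patient who attends one session and one visit and then complies poorly.

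| Text | Is the patient analysed? |
|---|---|
| 2.9, full analysis set | Yes: randomised, treated once, seen once |
| 2.3, second list, item ② | No: "the relevant data cannot be included in the final data analysis" |
| 2.9, per-protocol set | No, but this set is defined separately and section 2.3 does not refer to it |

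Nothing in the article says which statement prevails.

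**The plan's own figure.** Section 2.4 gives n = π(1−π)[(1.64+1.28)/δ]²(1+c)/c with π = 0.8, δ = 0.15, c = 1. This is 0.16 × (2.92/0.15)² × 2 = 121.3, rounded up to 122. Allowing for 10% dropout, 122/0.9 = 135.6, so 136 per arm and 272 in total. The figure reproduces and is not in dispute.

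**Illustration A: no true effect.**
- From the article: 136 per arm, chi-square test, significance at .05 (taken as two-sided). The common success rate p is 80% (π) or 72.5% (π − δ/2).
- Assumed, with no source in the article: the shares removed, and that removed patients succeed d = 25 points less often than those kept.
- Formula: if a share x is removed and those kept succeed at rate k, then p = (1−x)k + x(k−d), so k = p + xd. The bias is d times the difference in shares removed.
- Example: 10% removed from the Tai Chi arm only, p = 80%. Kept rate 80 + 0.10 × 25 = 82.5% (n = 122) against 80% (n = 136).
- Method: exact binomial enumeration of the uncorrected chi-square, counting significant results that favour Tai Chi.

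| Removed, Tai Chi v control | Bias, points | False claims for Tai Chi (p = 72.5% to 80%) |
|---|---|---|
| 0% v 0% | 0 | 2.6% |
| 10% v 10% | 0 | 2.5-2.6% |
| 10% v 5% | 1.25 | 4.1-4.4% |
| 15% v 5% | 2.5 | 6.6-7.3% |
| 20% v 5% | 3.75 | 9.8-11.4% |
| 10% v 0% | 2.5 | 6.6-7.5% |
| 15% v 0% | 3.75 | 10.0-11.5% |
| 20% v 0% | 5 | 14.2-17.0% |

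If removed patients succeed as often as those kept (d = 0), there is no bias whatever the shares.

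**Illustration B: item ③ under the planned effect.**
- Success rates 0.8 ± 0.075, that is 87.5% v 72.5%, with 136 per arm and the same test.
- Assumed: every removed patient is a non-success, with 2-3% removed under Tai Chi and 8-10% under control.
- Formula: visible rate = p/(1−x).

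| Removed, Tai Chi v control | Visible rates | Difference, points | Power |
|---|---|---|---|
| None | 87.5% v 72.5% | 15.0 | 88% |
| 3% v 8% | 90.2% v 78.8% | 11.4 | 73% |
| 2% v 8% | 89.3% v 78.8% | 10.5 | 65% |
| 3% v 10% | 90.2% v 80.6% | 9.7 | 60% |
| 2% v 10% | 89.3% v 80.6% | 8.7 | 50% |

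**The case against.** The best defence is that the second list is only a loosely worded description of the per-protocol set, since it resembles how such a set is built and section 2.9 has one. That may be the intention. But the list speaks of the final analysis without restriction, never mentions the per-protocol set, and is not overridden by a named primary set. What stands is that this is an unresolved conflict, not a settled decision to abandon intent-to-treat.

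A reader might infer more than the article supports:

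- **That only the Tai Chi arm can fail to comply.** Control patients also have several drug classes, health education and the trial-wide advice on smoking, alcohol, food and strenuous exercise. The text supports more opportunity for removal in the Tai Chi arm, not removal there alone. The one-arm rows of the first table are an extreme case.
- **That item ② removes patients according to how they did.** The phrase more naturally means compliance too poor for efficacy to be assessed, and section 2.5 keeps efficacy assessors unaware of group. The fair complaint is that there is no threshold and no named decision-maker.
- **That the rule makes a null trial look positive.** This holds only if removal is unequal and the removed patients do worse. Illustration B, with more progression under control, works the other way.

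**Conclusion.** The point holds. Section 2.3 states a rule that excludes randomised patients for post-randomisation reasons, it contradicts section 2.9, and it should be fixed before the analysis. The contradiction needs no assumption; the size of the bias does. The article gives no removal rates, no success rate among poor compliers and no progression rates, so every percentage in the two tables is conditional on the inputs shown. Within them, the consequence runs from no inflation at all (equal removal) through about 4-11% false claims for Tai Chi (unequal removal in both arms) to 7-17% (one-arm removal), against 2.6%. Item ③ could in the other direction take power from 88% to about 50-73%. The net direction cannot be predicted from the article.

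**What to change.** In section 2.3, delete the statement that data under items ① to ④ cannot be included in the final analysis, and say that these items define only the per-protocol set. All four items need this: leaving item ① in place would preserve the same conflict.

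In section 2.9, state that:

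- the primary comparison keeps all randomised patients in their assigned arm and decides the primary result;
- outcome visits are sought whatever the attendance, unless the patient withdraws consent to follow-up;
- patients whose disease progressed stay in and are graded as observed;
- the per-protocol analysis is supportive, with compliance defined from sessions attended and fixed before outcomes are linked to arm.

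The cost is a change of wording in two sections and continued outcome visits for patients who stop Tai Chi. The observed effect may be somewhat smaller because poor compliers stay in. Visits cannot be guaranteed for patients who withdraw, so some outcomes will still be missing.

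### Section 2.3 bars enrolled patients who meet any of four post-enrolment criteria from the final analysis, which conflicts with the intent-to-treat full analysis set in section 2.9

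*Protocol article*

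**What the plan says.** Section 2.3 (Patients) of the protocol article has two exclusion lists. The first concerns eligibility. The second is introduced as "A criterion used to screen patients who have become experimental subjects, but the relevant data cannot be included in the final data analysis". Its four items are:

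1. "Severe adverse events or serious complications are not suitable for the next test"
2. compliance so poor that neither benefit nor harm can be judged properly
3. "The disease progresses during the treatment process, and the treatment plan needs to be changed"
4. withdrawal at the patient's request, for any reason.

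Section 2.9 (Statistical analysis plan) defines the main set this way: "The full analysis set refers to the intent-to-treat analysis of all subjects randomly enroll, treat at least once and visit at least once". It makes no exception for any of the four items. It then defines a second set: "Per-protocol set: includes all subjects who comply with the trial protocol, have no missing baseline variables, and can measure the main variables". That definition does not refer to the list in 2.3.

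Section 2.6.1 defines the primary outcome from the change in NYHA class: "total effective rate = (marked effective number + effective number)/total number", expressed as a percentage.

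**The concern.** The second list in 2.3 acts after randomisation and is not tied to any analysis set. Read as written, it overrides the intent-to-treat principle that 2.9 adopts.

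The criteria are not neutral with respect to the outcome. A patient with a serious complication, or whose disease progresses so that treatment must change, is plausibly less likely to improve by an NYHA class. Such a patient would then count in the denominator of the total effective rate but not in the numerator. Removing patients of this kind raises the rate in their arm.

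The comparison between arms is affected when the share removed, or the kind of patient removed, differs by arm. If Tai Chi itself changes how often patients progress, have complications or stop, then removal discards part of the effect that the trial sets out to measure. Blinded efficacy assessment (section 2.5) does not protect against this, because the problem lies in who is analysed and not in how the outcome is rated.

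**Working it through.** **Step 1: the two rules side by side.** Take a patient who is randomised, starts treatment, attends the week-12 assessment (section 2.7) and then meets one of the four criteria.

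| Event after week 12 | Full analysis set, 2.9 | Final analysis, 2.3 |
|---|---|---|
| Severe adverse event or complication | in | out |
| Poor compliance | in | out |
| Progression with a needed treatment change | in | out |
| Withdrawal on request | in | out |

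All four items conflict in the same way. There is no conflict only for patients who leave before any treatment or visit, since 2.9 does not count them either. The article does not say that 2.3 applies to the per-protocol set alone, and 2.9 does not name the set for the primary comparison, so neither section settles the matter.

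**Step 2: the plan's own figures.** Section 2.4 gives quantiles 1.64 and 1.28, π = 0.8, δ = 0.15 and c = 1:

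- n = 0.8 × 0.2 × (2.92/0.15)² × 2 = 121.26, rounded up to 122 per arm.
- With 10% dropout: 122/0.9 = 135.6, rounded up to 136 per arm, 272 in total.

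Both match the article. The sample size is not in question. It supplies 80% and 136 per arm for the illustrations.

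**Step 3: what removal does to a rate.** Let p be the effective rate with everyone kept, e the share of an arm removed, and r the share of those removed who would have been effective. Then

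analysed rate = (p − e·r)/(1 − e).

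Assumptions, none of them from the documents: p = 0.80 (equal to π in 2.4), a total of 5% to 10% of patients open to removal (the upper value borrowed from the dropout allowance), and r = 0 or 0.5.

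(a) *All such patients removed, same share in both arms.*
- r = 0: 0.80/0.95 = 84.2%; 0.80/0.90 = 88.9%.
- r = 0.5: 0.775/0.95 = 81.6%; 0.75/0.90 = 83.3%.
- The difference between arms stays at zero.

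(b) *A true effect that acts only through the removed patients.* Suppose 10% of controls and 5% of Tai Chi patients meet a criterion, none of them effective, and the rate among the rest is 0.80/0.90 = 88.9% in both arms.
- True rates: 0.90 × 0.889 = 80.0% and 0.95 × 0.889 = 84.4%, a difference of 4.4 points.
- After removal: 88.9% and 88.9%, a difference of 0.
- With the arms exchanged, a harm of the same size disappears.

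(c), (d) *No true effect, uneven removal.* A share q of each arm meets a criterion. The fraction of those actually removed is 60% in one arm and 40% in the other (c), or 75% and 25% (d), so e = q × fraction. False-positive rates come from exact binomial enumeration of the uncorrected two-sided chi-square test at P < .05, with arm sizes after removal rounded to whole patients. Differences are taken from unrounded rates.

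| Split | q | r | Analysed rates | Shift, points | False-positive rate |
|---|---|---|---|---|---|
| 60/40 | 5% | 0 | 82.5% vs 81.6% | 0.8 | 5.4% |
| 60/40 | 10% | 0 | 85.1% vs 83.3% | 1.8 | 6.7% |
| 60/40 | 5% | 0.5 | 80.9% vs 80.6% | 0.3 | 5.1% |
| 60/40 | 10% | 0.5 | 81.9% vs 81.3% | 0.7 | 5.2% |
| 75/25 | 5% | 0 | 83.1% vs 81.0% | 2.1 | 7.3% |
| 75/25 | 10% | 0 | 86.5% vs 82.1% | 4.4 | 16.4% |
| 75/25 | 5% | 0.5 | 81.2% vs 80.4% | 0.8 | 5.3% |
| 75/25 | 10% | 0.5 | 82.4% vs 80.8% | 1.7 | 6.3% |

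With no removal (136 vs 136), the same test rejects in 5.1% of trials.

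**The case against.** The best defence is that the 2.3 list was meant to feed the per-protocol set. Section 2.9 defines three sets in the usual way, and poor compliance in 2.3 fits the per-protocol requirement to comply with the protocol. A condensed article might leave the mapping of withdrawals to analysis sets to the full protocol. This makes the conflict look like loose wording, but it does not remove it. Section 2.3 refers to the final analysis without limit, and a fuller document could follow one section only by overriding the other.

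The magnitudes are also open to challenge. Every removal and response rate above is assumed. The largest false-positive rate needs 10% meeting a criterion, a 75/25 split and no responders among those removed. With half responding, the rates stay between 5.1% and 6.3%. That objection stands.

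A reader might infer more than the documents support:

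- *That the progression criterion is the particular fault.* All four criteria share the defect, and nothing shows that progression would remove more patients than poor compliance or withdrawal. Section 2.3 enrols only stable patients and excludes those at high risk.
- *That progression is the same as the worsening category of the primary outcome.* That category reads "Deterioration: the deterioration of heart function is less than grade 1", which taken literally does not cover a full-grade worsening. Progression could also be a new ischaemic event with NYHA class unchanged at week 24. The link to the outcome is plausible but remains an inference.
- *That the lack of a definition of progression is an error.* An article commonly leaves such a definition to the full protocol.
- *That the rule favours Tai Chi.* Nothing in the text shows that removal would differ by arm, and the bias could go either way.

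**Conclusion.** Wrong as written. Sections 2.3 and 2.9 give incompatible rules on whether randomised, treated and visited patients are analysed once they meet any of four post-enrolment criteria. Following 2.3 would remove patients for reasons that arise after randomisation and are plausibly related to the outcome.

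The size of the effect cannot be determined from the documents. It is likely to raise the effective rate reported in each arm, provided that the patients removed respond less often than the rest. The comparison is biased only if the patients removed differ by arm in number or kind. With equal shares of similar patients removed, the bias in the comparison is zero. The figures in the working show what could happen under stated assumptions and are not estimates for this trial.

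**What to change.** In section 2.3, retitle the whole second list (all four items) as reasons for stopping study treatment or for exclusion from the per-protocol set. Replace the reference to the final analysis with the per-protocol set.

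In section 2.9, state that the primary comparison of the total effective rate uses the full analysis set as already defined there, with patients in their assigned arm and the week-24 NYHA outcome as assessed, whatever treatment change occurs. State also that full-analysis-set patients without a week-24 assessment stay in the denominator under one rule, for example counted as not effective. The set need not be widened to all randomised patients to resolve this conflict.

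The cost is a few words in 2.3 and one or two sentences in 2.9. Patients who stop or change treatment must still be assessed at week 24, a time point already planned in section 2.7. The sample size stays at 272. The downside for the sponsor is a possibly less favourable effective rate.

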### Sample size

2.4

According to the calculation formula:

$${\text{n}}_{1}=\pi (1-\pi ){\left[\frac{\left(\mu_{1-\alpha }+\mu_{1-\beta }\right)}{\delta }\right]}^{2}\frac{\left(1+\text{c}\right)}{\text{c}},{\text{n}}_{2}=\text{c}{\text{n}}_{1}$$

Using the superiority test, $\mu_{1-\alpha }=1.64,\mu_{1-\beta }=1.28.\pi =0.8,c=1,\delta =0.15$, calculate n1 = n2 = 122. Considering the clinical dropout rate of about 10%, a total of 272 cases need to be included. The included patients will be numbered according to the order of visits, and will be divided into an experimental group and a control group using a completely random method, with 136 cases in each group.

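### The sample size assumes a one-sided 5% test, but the planned chi-square test at P<.05 is two-sided, so 122 per arm gives about 83% power rather than 90%

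*Protocol article*

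**What the plan says.** Section 2.4 (Sample size) describes a superiority test and gives a formula for two proportions. Its inputs are a normal quantile of 1.64 subscripted 1−α, a quantile of 1.28 subscripted 1−β, π = 0.8, c = 1 and δ = 0.15. From these the authors "calculate n1 = n2 = 122". They then inflate for losses: "Considering the clinical dropout rate of about 10%, a total of 272 cases need to be included", which is 136 per group.

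Section 2.6.1 makes the primary outcome binary: "Main efficacy indicators: total effective rate".

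Section 2.9 (Statistical analysis plan) fixes the test, "Chi square test will be used for counting data", and sets P < .05 as the threshold for results "with statistical significance". It mentions neither a one-sided test nor a 0.10 two-sided level, and nothing else in the article links this threshold to the 1.64 used in section 2.4.

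**The concern.** A sample size calculation and the analysis it supports should use the same error rate. Here 1.64 is the one-sided 5% point of the normal distribution. The 1−α subscript (not 1−α/2) shows that this was deliberate and not a slip. For a two-by-two table the chi-square statistic is the square of a z statistic, so P<.05 means |z| > 1.96.

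The primary analysis therefore has to clear a higher bar than the one the trial was sized for. What is at stake is power: the chance of missing a true 15-point benefit is larger than the 10% that the inputs imply.

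**Working it through.** **Inputs, all from section 2.4:** critical value 1.64, power quantile 1.28 (90%, implied by the value and not stated in words), π = 0.8, δ = 0.15, c = 1, dropout about 10%. From section 2.9: chi-square test, P<.05, hence a critical value of 1.96.

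**1. The protocol's own figure**

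n = π(1−π) × [(z_α + z_β)/δ]² × (1+c)/c

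= 0.8 × 0.2 × (2.92/0.15)² × 2 = 121.3, rounded up to 122.

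Dropout: 122/0.9 = 135.6, rounded up to 136 per group, 272 in total. Both figures reproduce.

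**2. The same formula with the critical value of the planned test**

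n = 0.8 × 0.2 × ((1.96 + 1.28)/0.15)² × 2 = 149.3, rounded up to 150 per group.

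With 10% dropout: 150/0.9 = 166.7, rounded up to 167 per group, 334 in total. The stated 122 is reached only with the one-sided value.

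**3. Power at the planned size, with the formula's variance**

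Power = Φ(δ/√(2π(1−π)/n) − z_crit)

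For n = 122: √(0.32/122) = 0.0512 and 0.15/0.0512 = 2.929.
- One-sided 5%: Φ(2.929 − 1.645) = Φ(1.284) = 90.0%
- Two-sided 5%: Φ(2.929 − 1.960) = Φ(0.969) = 83.4%

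For n = 136 (no losses): √(0.32/136) = 0.0485 and 0.15/0.0485 = 3.092.
- Two-sided 5%: Φ(3.092 − 1.960) = Φ(1.132) = 87.1%

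**4. Difference detectable with 90% power, two-sided, n = 122**

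(1.960 + 1.2816) × √(0.32/122) = 3.2416 × 0.0512 = 0.166, or 16.6 points.

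**5. Sensitivity to the meaning of π = 0.8**

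The article gives no arm rates, so each pair below is an assumption. All have a 15-point difference and 122 per arm.

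| Assumed rates (control vs Tai Chi) | Meaning of 0.8 | One-sided 5%, normal approximation | Two-sided 5%, normal approximation | Two-sided 5%, exact (uncorrected chi-square) |
|---|---|---|---|---|
| 72.5% vs 87.5% | mean of the two arms | 90.4% | 83.8% | 84.8% |
| 65% vs 80% | Tai Chi rate | 84.0% | 75.0% | 75.5% |
| 80% vs 95% | control rate | 97.4% | 94.8% | 96.1% |

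In every row the two-sided test has less power than the one-sided test. How far the result lies from 90%, and on which side, depends on the row.

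**The case against.** The strongest defence is that section 2.4 does not hide its choice: it names a superiority test and subscripts 1−α. One-sided sizing is legitimate, section 2.9 never uses the word two-sided, and a fuller plan not shown here could declare a one-sided primary test. This stands to the extent that the authors could resolve the mismatch in either direction. It does not remove the mismatch, because the article itself states both the sizing quantile and the test with its threshold, and an ordinary chi-square test at P<.05 is non-directional.

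A second objection is that 83% depends on how π is read. That is correct, and if 0.8 is the control rate, power exceeds 90% even for a two-sided test. The common-rate reading is the natural one, since the formula puts a single π into the variance for both arms. Still, 83% is a conditional figure and should be given as such.

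Third, the practical loss is modest: 83% is above the 80% often accepted as a minimum, and no one proposes to change the design. This also stands, and it limits the weight of the point.

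A reader might go further and infer that the false-positive rate is inflated, or that a two-sided p between .05 and .10 could be called positive or negative after the data are seen. The article does not support this. Section 2.9 fixes the test and the threshold, so such a result is not significant, and no passage proposes to halve the p-value. Nor is the article at fault for not naming the version of the chi-square test; that detail belongs in a statistical analysis plan.

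**Conclusion.** The point holds as an inconsistency between sizing and analysis. It is not an arithmetic error: 122 and 272 follow correctly from the stated inputs. The planned primary test does not deliver the 90% power those inputs imply. With π = 0.8 as the common rate and a 15-point difference, power is about 83% with 122 evaluable per arm, so the type II error is about 17% instead of 10%. It is still below 90%, at 87%, if no one is lost.

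These figures rest on two assumptions: that P<.05 carries its usual two-sided meaning for a chi-square test, and that 0.8 is the common rate. On the other two readings of 0.8, exact two-sided power is about 76% or 96%. The consequence is confined to power. It should be corrected, but it does not threaten the validity of the trial's test.

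**What to change.** Keep 272 patients. In section 2.4, state that the primary test is two-sided at 0.05, and restate the power as about 83% for a 15-point difference around a common rate of 0.8 with 122 evaluable per arm. Equivalently, state a detectable difference of about 16.6 points at 90% power. State the control and Tai Chi rates that the authors actually assumed. If 0.8 was meant as one arm's rate, the power should be recomputed from that pair; 72.5% vs 87.5% should not be written in as the trial's assumption unless the authors confirm it.

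The cost is a sentence or two and a slightly less favourable stated power, with no added patients. Holding 90% power for the two-sided test would instead take 150 evaluable per arm, 334 in total after 10% dropout, which is 62 more than planned. A one-sided 5% primary test would also restore consistency, but section 2.9 would have to declare and justify it in advance.

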**Methods::**

This is a prospective randomized controlled trial. 272 patients with myocardial infarction will be randomly divided into an experimental group and a control group according to 1:1, with 136 cases in each group. The control group: conventional treatment; the experimental group: increase Tai Chi exercise on the basis of the control group. Both groups will receive standard treatment for 24 weeks and will be followed up for 3 months. Observation indicators include: total effective rate, 6 minutes walking test, brain natriuretic peptide, left ventricular ejection fraction, the adverse reaction rate, etc. The data will be analyzed by using SPSS 25.0 software.

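### Unstratified allocation leaves baseline NYHA class unbalanced, although class I patients cannot meet the primary response definition

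*Protocol article*

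**What the plan says.** Section 2.4 (Sample size) describes the allocation. "The included patients will be numbered according to the order of visits", and they are then split between the two arms "using a completely random method, with 136 cases in each group". The Methods part of the abstract says the same: patients are "randomly divided into an experimental group and a control group according to 1:1, with 136 cases in each group". Neither place names a stratification factor.

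Section 2.3 (Patients) admits "Cardiac function grade I to III". In Section 2.6.1 (Efficacy indicators) the primary endpoint is the total effective rate, which counts patients who are markedly effective or effective by change of NYHA grade. The lower threshold is "Effective: cardiac function improved by grade 1, but not as good as grade 2"; the higher one is about two grades.

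Section 2.9 (Statistical analysis plan) assigns the chi-square test to counting data and names no adjustment for baseline class.

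**The concern.** NYHA class at entry is more than a prognostic factor here, because it decides who can respond at all. A class I patient has no better grade to move to and is a non-responder by construction. A class II patient can improve by one grade. Only a class III patient can improve by two.

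If one arm happens to receive more class I patients, its total effective rate falls for a reason unrelated to Tai Chi. An unstratified allocation does nothing to prevent this, and an unadjusted chi-square test does nothing to correct it. At stake is how far the primary comparison can be trusted in a single trial whose planned difference is 15 points.

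**Working it through.** **The plan's own figure.** The inputs in Section 2.4 are quantiles 1.64 and 1.28, π = 0.8, c = 1 and δ = 0.15.

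- n = 0.8 × 0.2 × [(1.64 + 1.28)/0.15]² × 2 = 121.26, rounded up to 122 per arm.
- With 10% dropout, 122/0.9 = 135.6, rounded up to 136 per arm, or 272 in total.

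The stated sample size reproduces.

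**Arm sizes under the two readings of the method.**

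- Coin-tossing: arm size is Binomial(272, 0.5), with SD √272/2 = 8.2 and a 95% range of 120 to 152. The chance of exactly 136:136 is 4.8%.
- A random list with fixed totals: 136:136 is certain.

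Neither balances NYHA class. The simulated SD of the class imbalance is nearly identical for both (4.85 and 4.86 points at a 20% class I share).

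**Assumed class I share.** The article gives no share f. If class I cannot respond, the overall response is at most 1 − f, so a planned 0.8 implies f of at most 20%. I take f = 10% to 20%.

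**Imbalance in the class I share.** SD = √[2f(1 − f)/136].

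- f = 10%: √(0.18/136) = 3.64 points; 95% range ±1.96 × 3.64 = ±7.1 points.
- f = 20%: √(0.32/136) = 4.85 points; 95% range ±1.96 × 4.85 = ±9.5 points.

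With fixed totals, a gap of 5 points or more arises in about 22% of trials at f = 10% and 29% at f = 20%. A gap of 10 points or more arises in about 0.4% and 5%.

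**Shift in the response difference.** Shift = imbalance × r, where r is the response rate in classes II and III (assumed).

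| Class I share | 95% imbalance | Shift, r = 80% | Shift, r = 90% |
|---|---|---|---|
| 10% | ±7.1 | ±5.7 | ±6.4 |
| 20% | ±9.5 | ±7.6 | ±8.6 |

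Against the planned 15 points, 5.7/15 = 38% and 8.6/15 = 57%. If the overall response is held at exactly 0.8, then r = 0.8/(1 − f). This is 0.889 at f = 10% (shift ±6.3) and 1.0 at f = 20% (shift ±9.5, the limiting case in which every class II and III patient responds).

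**Precision lost.** At f = 10% and r = 0.889, the outcome variance is 0.8 × 0.2 = 0.16. The part due to class I versus the rest is f(1 − f)r² = 0.09 × 0.790 = 0.071, which is 44% of the total. A stratified design and analysis can remove this part.

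**Type I error.** Simulating the unadjusted two-sided 5% test under no effect, with class I as certain non-responders at shares of 20% and 30%, gave an overall error of 4.6% to 5.4%. At f = 20% and r = 90%, the error was about 46% to 47% among trials with a class I gap of 10 points or more. Those are the roughly 4% to 5% of trials that turn out badly balanced.

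**The case against.** The strongest reply is that unstratified randomisation of 272 patients is valid. Chance variation in baseline class is already inside the π(1 − π) variance that produced 122 per arm, and the unadjusted test keeps its error rate. That stands: there is no bias and no error in the sample size. It does not make the choice efficient, because much of that variance comes from a factor known at entry.

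The class I share is also unknown, and 20% is a generous cap. If 0.8 is the average of two rates 15 points apart, the higher is 87.5% and the cap is 12.5%. If 0.8 is the control rate, the Tai Chi rate is 95% and the cap is 5%, where the imbalance is ±1.96 × √(0.095/136) = ±5.2 points and the shift no more than that. On the other hand, Section 2.3 does not limit class I enrolment, so the actual share may exceed any of these caps.

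Two stronger readings are tempting, and the document supports neither.

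- A reader might infer that the method contradicts 136 per group. A fixed-total random list fits the wording and gives exactly that. Even under coin-tossing, power by the plan's formula is 92.4% at 120:152 against 92.7% at 136:136.
- A reader might infer that recruiters can foresee and steer allocations. Nothing says who holds the list, and an article may leave concealment to the full protocol. Consent precedes randomisation (Section 2.2), and efficacy assessors are unaware of group (Section 2.5).

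An analysis plan that is not shown might adjust for NYHA class. The article nevertheless names the allocation method and the test, and these can be judged as stated.

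**Conclusion.** The point holds as an inexpensive improvement to a valid design. Under either reading, the stated allocation leaves baseline NYHA class to chance, while the endpoint makes class I patients certain non-responders and the stated test ignores class.

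With a class I share of 10% to 20% and a class II–III response of 80% to 90% (both assumed), chance imbalance moves the response difference by about ±6 to ±9 points at the 95% limits. A reader might take the ±7 to ±9.5 points of class imbalance as an effect comparable to the planned 15. That is not supported: those points are imbalance in the class share, and the resulting shift in response is roughly half of 15 at the extremes and smaller in most trials. The consequence is avoidable loss of precision and, occasionally, a misleading result. Overall type I error remains near 5%.

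**What to change.** In Section 2.4, replace "using a completely random method, with 136 cases in each group" with: 1:1 randomisation in permuted blocks of randomly varying size, stratified by baseline NYHA class (I, II, III), with about 136 patients per group.

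In Section 2.9, analyse the primary response stratified by baseline NYHA class, for example by the Cochran-Mantel-Haenszel test, in place of the unadjusted chi-square test. Both changes are needed, since an unadjusted test would not use the balance that stratification provides.

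The cost is a stratified list to prepare, and final totals that may differ from 136:136 by a few patients because of incomplete blocks. NYHA class is already assessed for eligibility, so no extra patients, visits or measurements are required.
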